#### Aim

The aim of this mixed methods study is to: i) determine if the use of the targeted theory-informed interventions from the PREDICT Bronchiolitis KT Study have been effective at sustaining improvements (adherence to the Australasian Bronchiolitis Guideline i.e. no use of salbutamol, glucocorticoids, antibiotics, adrenaline and CXRs) in the care of children with bronchiolitis during the acute care period (first 24 hours of hospital presentation including ED and paediatric inpatient unit care) 1 and 2 years post-trial completion, specifically in 2018 and 2019, at intervention group hospitals; ii) determine if there are any improvements to adherence to the Australasian Bronchiolitis Guideline in control group hospitals; iii) understand the factors that influence the sustainability of improvements in intervention group hospitals and; iv) explore factors which may have contributed to improvements at control group hospitals. We will use an a priori definition of sustainability (see Data analysis below).

## Methods

### Study design

A mixed-methods study design will be used. Retrospective medical record audits will assess the sustainability of the improvements, and qualitative semi-structured individual or group interviews will assess the sustainment of the interventions.

### Setting/hospital selection

The original twenty-six hospitals (Australia = 20 and New Zealand = 6) which participated in the 2017 PREDICT Bronchiolitis KT Study will be invited to participate [4]. Hospitals must be able to meet local governance requirements and collect the required data regarding bronchiolitis care from the medical records within a specified timeframe (e.g. 6 months following local governance approval).

Clinical Directors of EDs or general paediatric inpatient units whose hospital participated in the PREDICT Bronchiolitis KT Study will be approached by email to assess interest and capacity for their hospitals to be involved in this study [4]. The research team will send an invitation email, an information statement, and an expression of interest form to eligible hospitals. Clinical Directors will be encouraged to discuss the study with relevant personnel in their departments. Phone and email contact will be made by the research team approximately 1 week after sending the recruitment pack to check receipt and ascertain interest. A site meeting will be arranged (via face-to-face or telephone) with relevant stakeholders in the ED and paediatric inpatient unit to discuss details and logistics of the study. Hospitals will only be able to participate in the qualitative semi-structured individual or group interviews if they have agreed to conduct the retrospective medical record audit.

#### Quantitative study

##### Selection of patients with bronchiolitis

A retrospective patient medical record audit will be conducted by designated site study staff at each consenting site, under the supervision of site Principal Investigators. A list of all infants who presented between 1 January 2018 and 31 December 2019 with International Classification of Diseases 9th and 10th revision (ICD-9 or ICD-10) discharge codes for bronchiolitis (Table 2) will be retrospectively identified. To be eligible for inclusion, patients must be: aged less than 1 year (at time of presentation); AND have both an ED and discharge diagnosis of bronchiolitis. There are no patient-level exclusion criteria.

**Table 2 Tab2:** International Classification of Diseases (ICD) codes used for identifying patients

ICD code		Description
ICD–10	J21	Acute bronchiolitis
	J21-0	Acute bronchiolitis due to respiratory syncytial virus
	J21-1	Acute bronchiolitis due to human metapneumovirus
	J21-8	Acute bronchiolitis due to other specified organisms
	J21-9	Acute bronchiolitis, unspecified
ICD-9	466-11	Acute bronchiolitis due to respiratory syncytial virus
	466-19	Acute bronchiolitis due to other infectious organisms

Data for a total of 1800 infants (approximately 150 infants per site) will be collected at 2 years post-trial (2019), to address the primary outcome. Similarly, data from 1800 infants will be collected at one-year post-trial (2018). If a site has less than 150 infant presentations per year, 100% of eligible infants will be selected. If a site has more than 150 infant presentations per year, a random sample of 150 infants per year will be selected by an independent statistician using computer software.

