#### The PREDICT Bronchiolitis KT Study

The ‘Knowledge Translation (KT) in Australasian Paediatric Acute Care Settings Study’ (PREDICT Bronchiolitis KT study) (ACTRN12616001567415) was a multi-centre, cluster randomised controlled trial conducted in 26 Australian and New Zealand hospital Emergency Departments (EDs) and paediatric inpatient areas during the 2017 Southern Hemisphere bronchiolitis season (1st May to 30th November 2017), involving 3240 infants [4]. Of the 26 hospitals, 13 were randomised to the intervention group and 13 to the control group with all hospitals completing the trial. The intervention group received targeted, theory-informed interventions developed to address factors identified as influencing bronchiolitis management in Australia and New Zealand [32]. Interventions consisted of: identification of stakeholder meetings; clinical leads; Train-the-trainer workshop; educational materials with scripted, targeted messaging; other educational material consisting of a clinician video demonstrating how to talk with families about bronchiolitis, promotional materials, evidence fact sheets; and finally monthly audit and feedback (Table 1) [4, 33]. Both intervention and control group hospitals received printed and electronic copies of the Australasian Bronchiolitis Guideline.

**Table 1 Tab1:** Implementation Strategy Components used in the PREDICT Bronchiolitis KT Study [4, 33]

Intervention Components	Intervention Hospitals	Control Hospitals Post Trial^a^
Clinical leads	Four clinical leads for the duration of the study, included a medical and a nursing lead from each emergency department and inpatient paediatric areas. Key tasks included attending a 1-day train-the-trainer workshop, spearheading educational intervention and other educational materials delivery to all staff, supervising monthly audit completion and delivery of feedback, and management of study requirements.	Encouraged to allocate a medical and nursing lead, but no further guidance provided.
Stakeholder Meetings	Study team presented the Australasian Bronchiolitis Guideline to clinical leads, discussed local and international bronchiolitis management variations, reviewed results of the local audit, and discussed any local anticipated barriers, with the aim to gain site buy-in.	Nil.

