#### Sample size

The sample size for this medical record audit will depend on the number of participating hospitals and will be recalculated upon completion of the hospital recruitment stage. Based on our previous study [4], assuming an Intra-cluster Correlation Coefficient of 0.11, an expected proportion of no use of all five low-value practices) of 85% (based on results of the PREDICT Bronchiolitis KT Study) [4] and a Coefficient of Variation of cluster sizes of 0.16 [4], a total sample size of 1800 (obtained from 12 intervention hospitals (clusters) with an average size of 150 infants) will achieve a confidence interval (CI) half-width of 7% (95%CI: 78 to 92%). An equivalent number of infants, i.e. 1800 in total, will also be obtained from ~ 12 control hospitals (clusters) with an average size of 150 infants.

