• The difference between control and intervention group hospitals in the proportion of infants presenting to hospitals with bronchiolitis who received care that adhered with each of the five individual Australasian Bronchiolitis Guideline Recommendations known to have no benefit^b^ in the acute care period: a) two- years (2019); following the completion of the PREDICT Bronchiolitis KT Study [4, 34]; and b) one- year (2018); following the completion of the PREDICT Bronchiolitis KT Study [4, 34];	
• The difference between control and intervention group hospitals in the proportion of infants presenting to hospital with bronchiolitis who received care that adhered with all five Australasian Bronchiolitis Guideline Recommendations known to have no benefit^b^ in the acute care period: a) two- years (2019) following the completion of the PREDICT Bronchiolitis KT Study (composite outcomes of all five practices) [4, 34]; and b) one- year (2018) following the completion of the PREDICT Bronchiolitis KT Study (composite of all five practices) [4, 34];	
• The trends in the proportions of infants presenting to hospital with bronchiolitis who received care that adhered with each of the individual five Australasian Bronchiolitis Guideline Recommendations known to have no benefit^b^ yearly from 2014 to 2019 in the acute care period, at control and intervention group hospitals [34].	

^a^ First 24 hours of hospitalisation, ^b^ no use of: i) salbutamol, ii) glucocorticoids, iii) antibiotics, iv) adrenaline, and v) chest x-ray

An a priori definition of sustained improvements will be based on the 7% median improvement achieved in the PREDICT Bronchiolitis KT Study [4]. Practices will be defined as sustained when there is either a maximum of a seven percentage point decrease or any level of improvement (i.e. -7% to infinity) from the participating hospital’s individual post-implementation results based on a composite outcome of the five low-value practices of interest [4, 34].

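### The sustained/not-sustained rule compares calendar-year 2018 and 2019 samples with a May-November 2017 reference, so seasonal differences count as loss or gain of benefit

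*Protocol article*

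**What the plan says.** In the Protocol article, the section on the PREDICT Bronchiolitis KT Study places the earlier trial "during the 2017 Southern Hemisphere bronchiolitis season (1st May to 30th November 2017), involving 3240 infants". The abstract gives the same months.

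The section on selection of patients takes its new frame from "A list of all infants who presented between 1 January 2018 and 31 December 2019". Within that frame, large sites contribute by this rule: "a random sample of 150 infants per year will be selected by an independent statistician using computer software". For small sites: "If a site has less than 150 infant presentations per year, 100% of eligible infants will be selected". Neither rule mentions months, and the section adds: "There are no patient-level exclusion criteria".

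The quantitative Data analysis section then defines practice as sustained when there is "either a maximum of a seven percentage point decrease or any level of improvement (i.e. -7% to infinity") relative to the hospital's "individual post-implementation results based on a composite outcome of the five low-value practices of interest". That section describes no matching by month, no restriction to the season and no seasonal adjustment.

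**The concern.** The rule subtracts a seven-month, in-season figure from a twelve-month figure. If clinicians use the five practices at a different rate for infants seen between December and April, the difference enters the 2017-to-2018 and 2017-to-2019 changes even when in-season practice has not moved. A larger sample does not remove it.

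The sustained label is the article's answer to its main question, and it is read hospital by hospital against a fixed 7-point margin. A hospital that has held its gains could be labelled as not sustained. If off-season adherence is the higher of the two, a real loss could be hidden.

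This is not a detail left to an analysis plan. The article fixes both windows, and they differ.

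**Working it through.** **Inputs from the Protocol article.** Reference window 1 May to 30 November 2017, with 3240 infants at 26 hospitals, or 3240/26 = 124.6 per hospital. Follow-up window: full calendar years 2018 and 2019, up to 150 infants per hospital per year. Margin 7 points. From the Sample size section: expected adherence 85%, ICC 0.11, coefficient of variation of cluster size 0.16, 12 hospitals of 150. The sustainability definition does not date the post-implementation result. I read it as the 2017 trial season, the only post-implementation period the article describes.

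**1. The plan's own figure.**
Design effect = 1 + ((1 + 0.16²) × 150 − 1) × 0.11 = 17.81.
Half-width = 1.96 × √(0.85 × 0.15 × 17.81 / 1800) = 6.96 points, against the stated 7. The sample-size statement is not at fault. It concerns the pooled proportion, not the change from 2017.

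**2. Window mismatch.** December to April is 5 of 12 months (151 of 365 days, 41%).

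**3. Artefact.** Let f be the share of the full-year sample presenting December to April, and d the in-season minus off-season adherence, in points.
Full-year adherence = in-season adherence − f × d, so
apparent change = true in-season change − f × d.
The article gives neither f nor d. The values below are assumptions:

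| f | d = 5 | d = 10 | d = 15 |
|---|---|---|---|
| 10% | 0.5 | 1.0 | 1.5 |
| 20% | 1.0 | 2.0 | 3.0 |
| 30% | 1.5 | 3.0 | 4.5 |

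This is 0.5/7 = 7% to 4.5/7 = 64% of the margin. If d is negative, the same sizes apply with the sign reversed. With cases spread evenly over the year (f = 5/12), the row would be 2.1, 4.2 and 6.3. The article itself names May-November as the bronchiolitis season, so f should be smaller than that. To use up the whole margin, d would have to be 7/0.20 = 35 points at f = 20%, or 7/0.30 = 23 points at f = 30%.

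**4. One hospital near the margin.** Take 125 infants in 2017, 150 in 2019, 85% in-season adherence in both years and no true change, with a normal approximation.
SE = √(0.1275/125 + 0.1275/150) = 4.32 points.
The chance that the observed change is no worse than −7 points is Φ(7/4.32) = 0.95. A 2-point spurious fall (2019 adherence 83%) lowers it to 0.87, and a 3-point fall (82%) to 0.81. With a true 3-point fall, the chance is 0.81 without the artefact, 0.67 with a further 2 points and 0.59 with a further 3.

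**5. Cost of restricting the months.** One hospital's 95% half-width at 85% adherence is 1.96 × √(0.1275/n): 5.7 points at n = 150, 6.3 at 125 and 6.8 at 105 (150 less 30%). For the change from 2017 with 105 infants in 2019, SE = √(0.1275/125 + 0.1275/105) = 4.73 points, and the chance in step 4 with no artefact becomes Φ(7/4.73) = 0.93 instead of 0.95.

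**The case against.** The dates are not in dispute. The case against concerns consequence.

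- The primary outcome, as worded under Outcome measures, is the 2019 proportion at intervention hospitals, and the study is sized on that proportion's confidence interval. Neither uses 2017 as comparator. The same-year intervention-control contrasts share one window. This stands, and it limits the point to the sustained classification.
- No seasonal difference in adherence is shown. This stands: the sign could go either way and could vary between hospitals. A reader might infer that the results are biased in a known direction at every hospital, but the article does not support that.
- Year-round care is a reasonable target, since the article counts follow-up in whole years from 30 November 2017. This stands for the proportion. It does not help a comparison whose other arm is in-season only.
- A reader might infer that the 2014-2019 trend breaks between 2017 and 2018. The article does not give the months of the 2014-2016 data, so the location of any break is unknown.
- A reader might think that restricting the months costs almost nothing, because the pooled half-width barely moves (6.96 points at 150 infants per hospital, 7.00 at 125). That figure is dominated by the ICC and is the wrong quantity here. The classification is made per hospital, where the loss in step 5 applies.
- An in-season analysis could sit in an analysis plan that is not shown. It could, but the rule as published compares unlike windows.

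**Conclusion.** The point holds for the sustained classification in 2018 and 2019. The published rule compares a calendar-year sample with a May-November reference and has no seasonal alignment. Under the assumed shares of 10-30% and differences of 5-15 points, the artefact is 0.5 to 4.5 points in either direction. Season alone is unlikely to use up the 7-point margin, but it can change the label for hospitals near it. The finding does not extend to the 2019 proportion as primary outcome, and it does not show that any bias is present. It is a comparability flaw of unknown size and sign, worth correcting because the correction is cheap.

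**What to change.** State in the Data analysis section that the sustainability comparison for 2018 and 2019 uses infants presenting 1 May to 30 November of the respective year. Report the full-year comparison as a sensitivity analysis. The year-round proportion can remain the outcome reported under Outcome measures. If presentation dates are held with the audit records, no new data are needed.

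The cost is a smaller number per hospital in that comparison, of the order shown in step 5. At larger sites this can be avoided by drawing the sample of up to 150 from in-season presentations. The year-round proportion would then need its own off-season records. Sites that already contribute all their infants cannot make up the loss, so their classification will be somewhat less precise.

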#### Outcome measures for quantitative study

Primary Outcome:Adherence with all five Australasian Bronchiolitis Guideline Recommendations (composite outcome) known to have no benefit (salbutamol, glucocorticoids, antibiotics, adrenaline and CXR) when an infant presents with bronchiolitis in the acute care period (first 24 hours of hospitalisation) at two- years (2019) following the completion of the PREDICT Bronchiolitis KT Study in intervention hospitals [34];

Secondary Outcomes:2.Adherence with all five Australasian Bronchiolitis Guideline Recommendations (composite outcome) known to have no benefit (salbutamol, glucocorticoids, antibiotics, adrenaline and CXR) when an infant presents with bronchiolitis in the acute care period (first 24 hours of hospitalisation) at one- year (2018) following the completion of the PREDICT Bronchiolitis KT Study in intervention hospitals [34];3.Adherence with all five Australasian Bronchiolitis Guideline Recommendations (composite outcome) known to have no benefit (salbutamol, glucocorticoids, antibiotics, adrenaline and CXR) when an infant presents with bronchiolitis in the acute care period (first 24 hours of hospitalisation) at 3a) one- year (2019) following provision of study materials, study results, and ‘Train the Trainer’ education (composite of all five practices) [4, 34]; and 3b) one- year (2018) following the completion of the PREDICT Bronchiolitis KT Study in control hospitals [4, 34].

The periods of one- and two- years following delivery of the intervention will be measured from the post-trial completion date of 30th November 2017.

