Train-the- trainer workshop	1-day workshop for clinical leads: discussed Australasian Bronchiolitis Guideline and evidence supporting recommendations, qualitative study identifying the facilitators and barriers of bronchiolitis management, implementation, and the development of interventions. Clinical leads received demonstrations on how to deliver educational interventions to their staff, outlines of study data timelines and requirements, and enabled planning time for clinical leads.	One-day workshop providing bronchiolitis intervention materials, with up to four clinical leads (medical and nursing) invited to attend. Discussion on what the aims of education materials were. Individual hospital data from the cluster RCT was presented (2014-2017). Feedback in relation to similar hospitals.
Educational intervention delivery	Key findings from qualitative study were presented in a PowerPoint with scripted messages stating use of behaviour change techniques most likely to effect change. Clinical Leads oversaw education delivery to medical and nursing staff using PowerPoint presentation. Within first month, aimed to educate 80% of staff and to ensure all staff educated ongoing education provided throughout duration of study.	PowerPoint presentation which was the same as presentation provided to the intervention hospitals.
Use of other educational materials	Clinical leads locally delivered promotional materials, evidence factsheets, clinician training video, and parent/caregiver information.	Education materials that were provided to the intervention hospitals.
Audit and feedback	Monthly audits of the first 20 bronchiolitis presentations, with report providing comparison between individual hospital results and top-performing site. Clinical leads disseminated report to their staff in written and verbal format; action planning with target setting encouraged.	Audit form and own hospital results from trial (4 years of data).
Ongoing facilitation	Weekly contact between clinical leads and study leads. Opportunities to ask questions via email.	Nil.

^a^delivered at trial completion in November 2018

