Findings of the PREDICT Bronchiolitis KT Study demonstrated that, when compared with control hospitals, intervention hospitals significantly improved adherence in management of bronchiolitis during the acute care period (first 24 hours of hospital presentation) for the five key low-value practices as per Australasian Bronchiolitis Guideline recommendations (14.1% adjusted risk difference, 95% CI, 6.5-21.7%; *P* < .001) [4, 34]. Specifically, during the acute care period (first 24 hours of hospital presentation), adherence to the Australasian Bronchiolitis Guideline recommendations with no use of salbutamol, glucocorticoids, antibiotics, adrenaline and CXRs, was 85% (95% CI, 82.6-89.7%) in the intervention group hospitals compared with 73% (95% CI, 65.3-78.8%) in the control group hospitals [4, 34]. At trial completion (November 2018), up to four nurses and doctors from each of the 13 control hospitals attended a 1 day workshop where they were given training and provided with intervention materials (Table 1). However, no on-going facilitation was provided.

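### As written, the 2018 control sample includes infants seen after the November 2018 control workshops, which slightly biases outcome 3b and the exploratory 2018 group difference

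*Protocol article*

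**What the plan says.** All places are in the protocol article.

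- **Sampling window** (Selection of patients with bronchiolitis): "A list of all infants who presented between 1 January 2018 and 31 December 2019" is compiled. At larger sites "a random sample of 150 infants per year will be selected by an independent statistician using computer software". For smaller sites, "If a site has less than 150 infant presentations per year, 100% of eligible infants will be selected". The section adds: "There are no patient-level exclusion criteria". No cut-off within 2018 is given.
- **Delivery of the control package** (The PREDICT Bronchiolitis KT Study): "At trial completion (November 2018), up to four nurses and doctors from each of the 13 control hospitals attended a 1 day workshop", where they received training and the intervention materials. The footnote to the control column of Table 1 agrees: "delivered at trial completion in November 2018".
- **Control outcomes** (Outcome measures for quantitative study): 3a is adherence "one- year (2019) following provision of study materials, study results, and ‘Train the Trainer’ education"; 3b is adherence "one- year (2018) following the completion of the PREDICT Bronchiolitis KT Study in control hospitals". The same section counts the one- and two-year periods from 30 November 2017.
- **Group difference** (Data analysis and Table 3): the difference between intervention and control hospitals in 2018 is an exploratory objective, as is that in 2019. Table 3 also labels the 2018 control sample as one year after delivery of the intervention, which does not fit a November 2018 delivery.

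**The concern.** Apart from the calendar year, what separates 3a from 3b is the package: 3a is defined by its provision and 3b is not. A 2018 window that stays open until 31 December admits control infants treated after staff had been trained and given the materials. If the package improves adherence, those infants raise the 2018 control proportion. Because the intervention group is expected to do better, they also shrink the 2018 group difference. The bias has a known direction and does not average out with more infants. At stake are one secondary sub-outcome (3b) and exploratory 2018 contrasts. The primary outcome (intervention hospitals, 2019) and secondary outcome 2 (intervention hospitals, 2018) contain no control infants and are not touched.

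**Working it through.** **Inputs from the article.** Case list from 1 January 2018; calendar 2018 has 365 days. Workshop in November 2018, day not given. Effect of the full intervention in the parent trial 14.1 points (95% CI 6.5 to 21.7). Control proportion in the parent trial 73%. ICC 0.11, coefficient of variation (CV) of cluster sizes 0.16, 12 hospitals of 150 infants per group, expected proportion 85%.

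**Step 1: the plan's own precision figure.** Design effect DE = 1 + ((1 + CV²) × m − 1) × ICC = 1 + (1.0256 × 150 − 1) × 0.11 = 17.81. Half-width = 1.96 × √(0.85 × 0.15 × 17.81 / 1800) = 6.96 points. The stated 7% is reproduced. The same formula gives
- 8.66 points for a control proportion of 73%;
- 11.1 points for the group difference, 1.96 × √[(0.85 × 0.15 + 0.73 × 0.27) × 17.81 / 1800].

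**Step 2: overlap in days.** Overlap = days after the workshop up to 31 December 2018, divided by 365.
- Workshop on 30 November: 31/365 = 8.5%.
- Workshop on 1 November: 60/365 = 16.4%.

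With presentations spread evenly over the year (an assumption), that is about 13 to 25 of 150 infants per hospital, or 153 to 296 of 1800.

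**Step 3: ceiling on the bias.** Bias = exposed share × package effect. The full 14.1 points acting at once is an upper assumption.

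| Share of 2018 control infants seen after the workshop | Infants of 1800 | Bias at 14.1 points | Bias at 6.5 / 21.7 points |
|---|---|---|---|
| 2% (assumed) | 36 | 0.3 | 0.1 / 0.4 |
| 5% (assumed) | 90 | 0.7 | 0.3 / 1.1 |
| 8.5% (even volume, 30 November) | 153 | 1.2 | 0.6 / 1.8 |
| 16.4% (even volume, 1 November) | 296 | 2.3 | 1.1 / 3.6 |

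The 2% and 5% rows are included because the article gives the 2017 bronchiolitis season as 1 May to 30 November, so December lies outside it. The true share is not stated.

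**Step 4: the other reading of year one.** If the year is counted from 30 November 2017 it ends on 30 November 2018, and the list still starts on 1 January, which leaves 334 days. The overlap is then at most 29/334 = 8.7% (bias 0.087 × 14.1 = 1.2 points), and nil if the workshop fell on 30 November.

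**Step 5: precision after restricting the control sample.** Losing 8% leaves 138 per hospital: DE = 1 + (1.0256 × 138 − 1) × 0.11 = 16.46, and 1.96 × √(0.73 × 0.27 × 16.46 / 1656) = 8.67 points against 8.66. Losing 25 of 150 leaves 125: DE = 14.99, and with N = 1500 the half-width is 8.70 points. Between-hospital variation dominates, so a few infants per hospital hardly matter.

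**The case against.** The strongest case on the other side has four parts.

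1. **The article does not state the intent.** A reader might infer that 3b is a defined pre-package outcome, that the 2018 difference was meant to be free of crossover, or that a planned 2018-to-2019 change in control hospitals is damaged. The documents do not support these readings. The article never calls 3b or the 2018 difference unexposed. It lists the 2018 and 2019 differences side by side without distinction. It plans no before-after contrast on the composite in control hospitals; the only time comparison is yearly trends for each individual practice. This stands, and the point is limited accordingly. What remains is that the article's own split of 3a from 3b by provision of the package does not match its sampling window.

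2. **The dates conflict.** Trial completion is November 2018 in the account of the parent study and in Table 1, but 30 November 2017 in the outcome section. If the package came at the 2017 completion, as Table 3's label could suggest, all of 2018 is post-package and no late-2018 cut-off helps. This also stands, as a reason to settle the dates first. November 2018 is the better supported delivery date, because two places state it and 3a, one year after provision in 2019, agrees with it.

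3. **The effect is tiny.** Control hospitals had no stakeholder meetings and no ongoing facilitation, and received an audit form with their own results in place of monthly audit and feedback. Even intervention hospitals aimed to educate 80% of staff over the first month. An immediate full effect in December is implausible. This stands and sets the low severity.

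4. **A cut-off in both groups for every outcome would cost intervention infants for no gain.** This stands. Outcome 2 should keep its full year.

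**Conclusion.** The point holds as a minor one. On the article's dates, some 2018 control infants presented after the control package arrived, and nothing in the text removes them. Outcome 3b is biased slightly upward and the exploratory 2018 group difference slightly towards zero. With even volume and the full 14.1-point effect at once, the bias is 1.2 to 2.3 points (0.6 to 3.6 across the confidence interval of that effect). A few tenths of a point is more likely, against half-widths of about 8.7 points for the control proportion and 11.1 for the difference, so it would not by itself change how either result reads.

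This rests on three assumptions: that delivery was in November 2018, that the 2018 sample means the calendar year (inferred from the two-year list and the per-year sampling), and that the package has some benefit.

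**What to change.** 1. Reconcile the dates and labels: trial completion (November 2018 or 30 November 2017), the date the control package was delivered, and the Table 3 label for the 2018 control sample. State the workshop date for each control hospital.
2. If delivery in November 2018 is confirmed, base outcome 3b on control infants who presented before their hospital's workshop date.
3. For the 2018 group difference, apply one calendar cut-off, before the first control workshop, to both groups so that the seasons match.
4. Keep the full-year 2018 sample for secondary outcome 2, and report the full-year control figure beside the restricted one.

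The cost is small, since the audit is retrospective and the list is drawn by presentation date. A few late-year infants are lost, which widens the control half-width from 8.66 to 8.67 points at 138 per hospital and to 8.70 at 125. The 2018 control window also becomes slightly shorter than the 2019 window, which should be noted wherever the two years are set side by side.
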